### Outcome parameters

The primary outcome parameter of this study is the number of patients with detected “epileptogenic” structural and functional brain abnormalities on 7 T and 9.4 T UHF neuroimaging, the so-called “diagnostic gain” in patients with 3 T MRI-negative drug-resistant focal epilepsy. The second primary outcome parameter is postoperative seizure outcome (ILAE/Engel class at 12 months) in operated UHF MRI-positive versus MRI-negative patients “i.e., therapeutic gain.”

As secondary outcome parameters, detection rate of UHF resting-state fMRI for cortical abnormalities in spontaneous blood oxygenation level-dependent (BOLD) signal fluctuations as a marker of an epileptogenic lesion, concordance of UHF MRI imaging with histopathological diagnosis of surgical specimen, intra- and inter-observer agreement for UHF MRI evaluation, and association between ROIs in the non- or semi-invasive work-up modalities and UHF MRI data will be assessed.

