**Methods:**

We present the EpiUltraStudy protocol to address the hypothesis that application of ultra-high field (UHF) MRI increases the rate of detection of structural lesions and functional brain aberrances in patients with drug-resistant focal epilepsy who are candidates for resective epilepsy surgery. Additionally, therapeutic gain will be addressed, testing whether increased lesion detection and tailored resections result in higher rates of seizure freedom 1 year after epilepsy surgery. Sixty patients enroll the study according to the following inclusion criteria: aged ≥ 12 years, diagnosed with drug-resistant focal epilepsy with a suspected epileptogenic focus, negative conventional 3 T MRI during pre-surgical work-up.

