## Introduction

About 30–40% of patients with epilepsy are drug-resistant, with higher rates for children [1]. Resective epilepsy surgery is a well-established, evidence-based, treatment option for 10–50% of drug-resistant patients, depending on the underlying etiology [2–4]. One of the major predictive factors for good surgical outcome (i.e., seizure freedom) is the detection of a potential epileptogenic lesion/zone on magnetic resonance imaging (MRI) [5–7]. Approximately 30% of adult and pediatric patients with focal epilepsy have no identifiable, potential epileptogenic lesion on MRI, “MRI-negative” [8–10]. Consequently, a considerable number of MRI-negative drug-resistant patients are not eligible for resective surgery, leading to continuation of disease burden and lower quality of life [9].

Recent developments in the field of non-invasive preoperative examinations, like high-density electroencephalography (EEG), EEG-functional MRI (fMRI), single photon emission computed tomography (SPECT), positron emission tomography (PET), magnetoencephalography (MEG), and ultra-high field (UHF) MRI, have improved localization of the epileptogenic zone, leading to surgical treatment in patients who previously were not considered candidates for epilepsy surgery [11–13]. The detection rate of potential epileptogenic lesions on MRI is strongly dependent on technical factors, such as magnetic field strength (in tesla, T), use of phased array head coils, and image (post)processing and analyses [9, 14]. Currently, the clinical state-of-the-art imaging for lesion detection in epilepsy includes a 3-T MRI dedicated epilepsy protocol, reviewed by an experienced neuroradiologist in the field of epilepsy(surgery) [15]. However, even under these optimal circumstances, small structural abnormalities, like focal cortical dysplasias (FCD), can remain unidentified at 3 T [16, 17]. FCDs are congenital malformations of cortical development characterized by aberrant migration and differentiation of neuronal cells [18, 19] and are a major cause of chronic epilepsy, especially in children [20]. It has been reported that FCD is the most frequent lesion (45–51%) in epilepsy surgery candidates who are “MRI-negative” at 3 T [17, 21], and cannot be visualized in up to 40% of the cases [22].

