We hypothesize that UHF MRI (7 T and 9.4 T) leads to improved detection and quantification of tiny structural and functional (sub)cortical abnormalities, due to a higher spatial resolution and contrast level beyond what is available at 3 T [23, 24]. By applying 9.4 T, we hypothesize that there will be an additional diagnostic gain compared to 7 T MRI. Additionally, this increased lesion detection of UHF MRI, and additional voxel-based morphometry postprocessing techniques of the UHF images, will guide surgical decision-making, leading to a more personalized type of epilepsy surgery and improved postoperative seizure outcome, with a higher chance of becoming seizure free in potential candidates for epilepsy surgery.

The primary objectives of this study are (1) to estimate the detection rate of structural and functional brain lesions on 7 T and 9.4 T MRI in patients with drug-resistant 3 T MRI-negative focal epilepsy and (2) to assess whether this increased detection rate is associated with improved postoperative seizure outcome. In this paper, we present the study protocol according to Standard Protocol Items: Recommendations for Interventional Trials protocol guidelines [25].

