The study participants’ timeline is outlined below; an overview is also given in Fig. 1.RecruitmentAll patients ≥ 12 years discussed in the epilepsy surgery workgroup will be analyzed for study eligibility. The treating physician will inform the patient about the main study characteristics, asked whether they, and in case of children the legal representative, is interested in more information and agrees to be contacted by phone by the investigator. Upon approval, the patient information letter (PIF) and informed consent form will be provided to the subjects. A minimum reflection time of 1 week is taken into account. Participants can contact the local investigator digitally. If no reply is received within 3 weeks, the investigator will contact the patient by phone. Patients will be informed that they can decide to end their participation at any time.Informed consentBefore performing the UHF MRI scan, a Dutch or German informed consent agreement form will be signed in duplicate for Dutch or German participants, respectively.Data recordingFollowing informed consent agreement, patient data will be recorded from digital patient files. Digital patient files encompass the electronic patient dossier (EPD) at the ACE MUMC + , ACE Kempenhaeghe, and RWTH Aachen University Hospital, containing the patient files from the multidisciplinary epilepsy surgery workgroup. MRI risk questionnaires will be filled out by patients and controlled by the MRI technician before performing MRI.MeasurementsAll patients will undergo 7 T MRI, and the first ten 7 T MRI-negative patients will undergo 9.4 T MRI on a different day than the 7 T scan, as described in the intervention protocol section.End of study for the participantDirectly following completion of the last UHF MRI scan, patients will have reached the end point of this study.Further recording of information

Data obtained by UHF MRI (part 4. Measurements) will be discussed in the multidisciplinary epilepsy surgery workgroup and, when consensus is reached about possible epileptogenicity of a novel lesion, stereo-EEG, respective, or minimally invasive surgery will be considered.

Results from the epilepsy surgery workgroup, surgery, histopathology, and postoperative seizure outcome at 1 year will be recorded from digital patient files. If patients do not undergo epilepsy surgery, conclusions, and recommendations from the workgroup, next to possible other treatment suggestions and seizure follow-up will be recorded.

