### Statistical analysis

Baseline characteristics of the cohort will be described in detail as mean and standard deviation or median and interquartile range for continuous variables (depending on their normality of distribution) and as count and percentage for categorical variables. Missing values are unlikely to occur, but in case of incomplete MRI data, we will use stochastic regression imputation to facilitate the inclusion of all study participants in the analyses.

UHF MRI data, such as characteristics of and, if applicable, localization of abnormalities, will be summarized using descriptive statistics. Primary outcomes diagnostic and therapeutic gain will be expressed as point estimates with 95% confidence intervals. Explorative analysis is used for quantitative MRI measurements (diffusion, fMRI, ASL). Radiological assessment will be done independently, in case of different results consensus will be sought. Intra-observer and inter-observer agreement in assessing MRI images will be quantified using Cohen’s kappa for categorical MRI parameters, and intra-class correlation coefficient (ICC) for continuous MRI parameters. Associations between qualitative findings and histopathological abnormalities will be computed using Spearman rank correlation, point bi-serial correlation, or Fisher’s Exact test, depending on the distribution of the findings.

We will assess the association between demographic, clinical parameters, and outcome measures by using univariable and multivariable regression analysis. A *p*-value of < 0.05 will be considered statistically significant. Statistical analysis will be performed using IBM SPSS software version 25 or higher.

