## Discussion

Patients with drug-resistant focal epilepsy, who are MRI-negative, are less likely to be considered candidates for surgery compared to MRI-positive patients and have less satisfactory seizure outcome after surgery [17, 39]. MRI-negative patients who do undergo surgery frequently have distinct epileptogenic lesions identified post-surgery via histopathological investigations or retrospective examination of the images [40, 41]. Therefore, it seems justified to conclude that improving detection rate for epileptogenic lesions improves postoperative seizure outcome.

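### The second primary outcome, labelled therapeutic gain, compares operated UHF-positive with operated UHF-negative patients: a prognostic association that cannot show what UHF MRI did for seizure outcome

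*Protocol article*

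**What the plan says.** The Outcome parameters section of the protocol article fixes the outcome: "The second primary outcome parameter is postoperative seizure outcome (ILAE/Engel class at 12 months) in operated UHF MRI-positive versus MRI-negative patients". It labels this therapeutic gain. Under Statistical analysis, "Primary outcomes diagnostic and therapeutic gain will be expressed as point estimates with 95% confidence intervals".

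The article words the purpose in two ways:

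- The abstract (Methods) is causal: "testing whether increased lesion detection and tailored resections result in higher rates of seizure freedom 1 year after epilepsy surgery". The hypothesis in the Introduction (UHF findings guide surgery and so improve outcome) and the study description under Study setting and population (therapeutic impact) point the same way. The opening of the Discussion goes further and infers that better detection improves outcome.
- Objective 2 in the Introduction is associational: "to assess whether this increased detection rate is associated with improved postoperative seizure outcome".

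On prognosis, the Introduction says: "One of the major predictive factors for good surgical outcome (i.e., seizure freedom) is the detection of a potential epileptogenic lesion/zone". The Discussion says that MRI-negative patients "are less likely to be considered candidates for surgery compared to MRI-positive patients and have less satisfactory seizure outcome after surgery".

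On selection, the section on recruitment, consent and timeline says that, after UHF results are discussed, "when consensus is reached about possible epileptogenicity of a novel lesion, stereo-EEG, respective, or minimally invasive surgery will be considered". The Intervention and evaluation protocol also places the choice between resection, S-EEG, RFTC and palliative options after the UHF result. For patients not operated, workgroup conclusions and recommendations, "next to possible other treatment suggestions and seizure follow-up will be recorded".

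**The concern.** Therapeutic gain would ordinarily mean the seizure outcome with UHF in the work-up set against the outcome without it. The fixed contrast does not measure that, for three reasons.

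1. **No comparator without UHF.** All participants are 3 T-negative and all have 7 T, so the MRI-negative patients in the definition can only be operated patients with a negative UHF scan. The contrast is lesion seen versus lesion not seen.
2. **The exposure is prognostic on the article's own account.** If patients with a visible lesion do better after surgery, a difference can arise even if UHF altered no operation.
3. **The analysed set is chosen partly by the test.** UHF findings feed the decision to operate, so the two operated groups reach surgery by different routes. A patient brought to surgery only because of UHF earns no credit for that step, and patients not operated are outside the contrast.

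The risk is that a positive difference is reported as therapeutic benefit, or a null one as lack of benefit, when neither reading follows.

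**Working it through.** **The plan's own figures.** Ten observations per variable times (5 confounders + 1 main variable) = 60, as stated. The half-width for a detection rate with n = 60 is 1.96 × √(p(1−p)/60): 0.118 at p = 6/19 (the previous 7 T series) and 0.127 at p = 0.50. Both are below the stated 0.20. These figures concern the detection rate. The article gives none for therapeutic gain.

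**Zero-effect contrast without UHF-driven selection.** The inputs are assumptions, not in the documents:

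- True lesion present in a share π of 0.40 or 0.50.
- UHF sensitivity s = 0.6; false-positive rate f of 0.05 or 0.15.
- Seizure freedom a with a lesion and b without, whether or not UHF shows it.

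Detection = πs + (1−π)f. The share with a true lesion is L₊ = πs/detection among UHF-positives and L₋ = π(1−s)/(1−detection) among UHF-negatives. The contrast is (L₊ − L₋)(a − b).

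| π | f | Detection | L₊ | L₋ | 0.6 vs 0.4 | 0.7 vs 0.4 | 0.7 vs 0.3 |
|---|---|---|---|---|---|---|---|
| 0.40 | 0.05 | 0.270 | 0.889 | 0.219 | 0.134 | 0.201 | 0.268 |
| 0.40 | 0.15 | 0.330 | 0.727 | 0.239 | 0.098 | 0.147 | 0.195 |
| 0.50 | 0.05 | 0.325 | 0.923 | 0.296 | 0.125 | 0.188 | 0.251 |
| 0.50 | 0.15 | 0.375 | 0.800 | 0.320 | 0.096 | 0.144 | 0.192 |

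So the contrast runs from about +0.10 to +0.27 with no UHF effect at all. It is 0 if a = b. The assumed detection rates bracket 6/19 = 0.316.

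**Zero-effect contrast with UHF-driven selection.** Take π = 0.50, s = 0.6, f = 0.05. Half the patients have a concordant other work-up, independent of UHF. The assumed probability of operation is 0.8 if UHF-positive. If UHF-negative it is 0.5 with a concordant work-up and 0.1 without. Seizure freedom is 0.3 + gL (lesion) + gC (concordant work-up), with no UHF term.

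- Share with a concordant work-up among operated UHF-positives: 0.5.
- Among operated UHF-negatives: 0.25/(0.25 + 0.05) = 0.833.
- Contrast = gL × (0.923 − 0.296) + gC × (0.5 − 0.833) = 0.627 gL − 0.333 gC.

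Results:

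- Only work-up prognostic (gL = 0, gC = 0.3): −0.10.
- Only lesion prognostic (gL = 0.3, gC = 0): +0.19.
- Both prognostic: from +0.03 (gL = 0.2, gC = 0.3) to +0.12 (gL = 0.3, gC = 0.2).

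The number operated would be 60 × 0.325 × 0.8 = 15.6 UHF-positive and 60 × 0.675 × 0.3 = 12.2 UHF-negative, about 28 in all.

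**Precision of the contrast.** Half-width = 1.96 × √(p₁(1−p₁)/n₁ + p₂(1−p₂)/n₂).

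- 15 vs 10 operated: 0.392 at 0.6 vs 0.4, and 0.382 at 0.7 vs 0.4.
- 14 vs 12 operated: 0.378 and 0.367.
- All 60 operated, split 19 vs 41 (60 × 6/19 ≈ 19): 0.266 and 0.255.

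At any plausible number operated, the interval is wider than the bias it would have to be separated from.

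**The case against.** The best defence is that objective 2 asks only about an association, and comparing operated UHF-positive with operated UHF-negative patients is a usable measure of one. That stands: the contrast is legitimate under that objective. What it does not support is the label or the causal wording in the abstract, the hypothesis and the study description.

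A reader might go further and infer that the outcome is bound to look positive even if UHF changed nothing, or that any difference is pure case mix. The documents support neither.

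- The statements on prognosis concern MRI-positive and MRI-negative patients in general. Nothing shows that lesions visible only at 7 T or 9.4 T, after an expert-reviewed negative 3 T scan, carry the same prognosis. The Challenges section itself warns of false positives.
- Operated UHF-negatives may be those with the strongest other evidence, which pulls the difference down and can reverse it.
- The Therapeutic value section gives a route to real benefit (better targeting, more complete lesionectomy), so the contrast mixes case mix with any effect.

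Two further points are fair but do not resolve the matter. Multivariable regression on up to five confounders may remove some case mix, but lesion visibility is the exposure itself and adjustment cannot supply patients managed without UHF. Non-operated patients do have follow-up recorded, so they leave this contrast but not the dataset. That makes a repair feasible, but it is not itself one.

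**Conclusion.** The concern holds in a limited form. The contrast is fixed as a primary outcome under a label it cannot bear: it has no comparator without UHF and is restricted to patients selected partly by the UHF result. On the article's own premise a difference may appear with no UHF effect. Its size and even its sign depend on selection: about +0.10 to +0.27 without UHF-driven selection and −0.10 to +0.19 with it. With 25 or 26 operated patients the half-width is about 0.37 to 0.39. All these values rest on assumed prevalence, sensitivity, prognosis and operation rates; the documents give none of them for this cohort. The structural point does not depend on them. Neither a positive nor a null result could be read as therapeutic gain, while the contrast remains usable as the association that objective 2 names.

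**What to change.** 1. Call the operated UHF-positive versus UHF-negative contrast a prognostic association and drop the term therapeutic gain for it. Bring the causal wording in the abstract, the Introduction's hypothesis, Study setting and population, and the opening of the Discussion into line with objective 2.
2. Record in the eCRF the surgery conference's plan (resection, S-EEG, RFTC or palliative) and target before UHF is disclosed, and again after. The multidisciplinary team already assesses eligibility in the pre-surgical work-up, so this documents decisions and does not change management.
3. Report over all 60 patients, with exact 95% CIs: (a) the proportion whose plan or target changed after UHF; (b) the proportion who had UHF-changed surgery and were seizure free at 12 months, counting non-operated patients as not gained. With n = 60 the exact half-width is about 0.13 when the proportion is one half (30/60).
4. Describe (b) as a whole-cohort yield, not a causal effect: some of those patients might have become seizure free under the pre-UHF plan.

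The cost is one extra eCRF field, revised wording, and a whole-cohort rate lower than the operated-only rate. The pre-disclosure plan has to be captured as the study runs, because one not documented then cannot be reliably reconstructed later.

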### Recruitment capacity, consent, and timeline

Recruitment of eligible study participants will take place at (1) both locations of the Academic Center for Epileptology (ACE) Kempenhaeghe/Maastricht University Medical Center + (MUMC +), Heeze/Maastricht, The Netherlands, and (2) the RWTH Aachen University Hospital, Section of Epileptology and Department of Neurosurgery Aachen, Germany. Based on feasibility and number of patients, we expect 30 patients from Kempenhaeghe/MUMC + , among which eight children 12 to 18 years, to qualify for this study annually. Recruitment from Aachen is expected to be 10 patients annually. Taking into account, a probable informed consent rate of 75% results in an annual inclusion of 30 patients.

The study participants’ timeline is outlined below; an overview is also given in Fig. 1.RecruitmentAll patients ≥ 12 years discussed in the epilepsy surgery workgroup will be analyzed for study eligibility. The treating physician will inform the patient about the main study characteristics, asked whether they, and in case of children the legal representative, is interested in more information and agrees to be contacted by phone by the investigator. Upon approval, the patient information letter (PIF) and informed consent form will be provided to the subjects. A minimum reflection time of 1 week is taken into account. Participants can contact the local investigator digitally. If no reply is received within 3 weeks, the investigator will contact the patient by phone. Patients will be informed that they can decide to end their participation at any time.Informed consentBefore performing the UHF MRI scan, a Dutch or German informed consent agreement form will be signed in duplicate for Dutch or German participants, respectively.Data recordingFollowing informed consent agreement, patient data will be recorded from digital patient files. Digital patient files encompass the electronic patient dossier (EPD) at the ACE MUMC + , ACE Kempenhaeghe, and RWTH Aachen University Hospital, containing the patient files from the multidisciplinary epilepsy surgery workgroup. MRI risk questionnaires will be filled out by patients and controlled by the MRI technician before performing MRI.MeasurementsAll patients will undergo 7 T MRI, and the first ten 7 T MRI-negative patients will undergo 9.4 T MRI on a different day than the 7 T scan, as described in the intervention protocol section.End of study for the participantDirectly following completion of the last UHF MRI scan, patients will have reached the end point of this study.Further recording of information

Data obtained by UHF MRI (part 4. Measurements) will be discussed in the multidisciplinary epilepsy surgery workgroup and, when consensus is reached about possible epileptogenicity of a novel lesion, stereo-EEG, respective, or minimally invasive surgery will be considered.

Results from the epilepsy surgery workgroup, surgery, histopathology, and postoperative seizure outcome at 1 year will be recorded from digital patient files. If patients do not undergo epilepsy surgery, conclusions, and recommendations from the workgroup, next to possible other treatment suggestions and seizure follow-up will be recorded.

### Sample size

The primary study outcome is the lesion detection rate of UHF MRI. This outcome will be estimated without formal null-hypothesis testing. We previously conducted a study in which we included 19 adult patients where MEG directed to an epileptogenic lesion [35]. All patients were 3 T negative; on 7 T, six patients showed possible epileptogenic lesions. However, as there is no similar research based on other examination modalities (SPECT, PET, etc.) available for UHF MRI imaging, no data to perform a sample size calculation is available [23, 24]. Therefore, we take a pragmatic approach to the determination of sample size. Rules of thumb for linear regression analysis state that at least 10 observations are needed for each variable that is entered in the regression model. In addition to univariate analysis, we aim to perform multivariable analysis in which we will correct for up to five potential confounding variables. Hence, we will need to include at least 60 patients for this study. With a sample of this size, the margin of error (i.e., half-width of the 95% confidence interval) of the detection rate will likely be below 0.20.

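### N = 60 rests on a linear-regression rule that fits neither primary outcome, so the claim that 60 patients support correction for five confounders does not stand

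*Protocol article*

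**What the plan says.** The Sample size section of the protocol article says that no prior data allow a formal calculation and that the approach is pragmatic. The derivation is then: "Rules of thumb for linear regression analysis state that at least 10 observations are needed for each variable". The planned model is a "multivariable analysis in which we will correct for up to five potential confounding variables", and the conclusion is "Hence, we will need to include at least 60 patients for this study". A closing sentence adds that the 95% CI half-width for the detection rate will probably be under 0.20. The Challenges section repeats that the number comes from observations per regression variable and leaves final power open.

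The Outcome parameters section defines what would be modelled. First: "The primary outcome parameter of this study is the number of patients with detected “epileptogenic” structural and functional brain abnormalities". Second: "The second primary outcome parameter is postoperative seizure outcome (ILAE/Engel class at 12 months) in operated UHF MRI-positive versus MRI-negative patients".

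The Statistical analysis section states: "We will assess the association between demographic, clinical parameters, and outcome measures by using univariable and multivariable regression analysis". It names no model type and sets significance at p < 0.05. Both primary outcomes are to be reported as point estimates with 95% confidence intervals.

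**The concern.** Ten observations per variable, counted over all patients, is a rule for a continuous outcome. A count of patients with a lesion is binary at patient level, and ILAE/Engel class is ordinal, or binary if reduced to seizure-free yes or no. No continuous primary outcome is defined. The denominator is a second difficulty: seizure outcome is compared among operated patients, while the rule is applied to all 60 enrolled.

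At stake is the adjusted analysis. The comparison of UHF-positive with UHF-negative operated patients is not randomised, so adjustment matters there. If the team relies on the statement that 60 is enough for five confounders, it may fit a model with too few outcome events per variable. The risks are overfitting, separation and unstable intervals, with results read at p < 0.05.

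**Working it through.** **Inputs from the protocol article**
- 10 observations per variable, up to 5 confounders, N = 60 (Sample size).
- Detection rate 6/19 = 31.6% in the team's earlier 7 T study (Sample size), and about 30% in earlier 7 T studies (Discussion and Conclusion).
- Seizure outcome is assessed in operated patients (Outcome parameters). Some patients will not have a resection (Intervention and evaluation protocol; timeline). The number operated is not given.

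**1. The plan's own figure.** 10 × (5 + 1) = 60, which reproduces exactly. Confounders alone give 10 × 5 = 50, which does not. The ceiling is therefore six variables: five confounders and one variable of interest.

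**2. The precision statement.** Wald half-width = 1.96 × √(p(1 − p)/60).
- p = 0.316: 0.118 (Clopper–Pearson 0.123 for 19/60).
- p = 0.50: 0.127 (Clopper–Pearson 0.132 for 30/60).

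The statement is true. A half-width of 0.20 needs only 1.96² × p(1 − p)/0.04 = 21 patients at 31.6%, or 25 at 50%, so this criterion did not set N.

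**3. Lesion detection as a binary outcome.** Events per variable = 60 × min(p, 1 − p)/6. N for ten per variable = 60/min(p, 1 − p).

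| Detection rate | Smaller group of 60 | Per variable, six variables | Variables at 10 each | N for 10 each | N for 5 each |
|---|---|---|---|---|---|
| 30% | 18 | 3.0 | 1 | 200 | 100 |
| 31.6% | 19 | 3.2 | 1 | 190 | 95 |
| 50% | 30 | 5.0 | 3 | 120 | 60 |

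The smaller group can never exceed half the sample, so 5.0 is the most that 60 patients can give for six variables at any detection rate.

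**4. Seizure outcome on the plan's own linear rule.** Six variables need 60 operated patients. With n operated the rule gives n/6 observations per variable: 45 give 7.5, 30 give 5, 15 give 2.5 (n assumed). With 60 enrolled, every patient not operated takes it below 10.

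**5. Seizure outcome dichotomised.** Assumed ranges, since the document gives none: 15–60 operated, 30–60% seizure-free.
- Lowest: 15 × 0.30 = 4.5 in the smaller group; 4.5/6 = 0.75 per variable.
- Highest: 60 × 0.50 = 30; 30/6 = 5.0 per variable.

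**The case against.** The strongest reply is that the regression is not the primary analysis. The detection rate is to be estimated without a formal test, both primary outcomes are reported with confidence intervals, and 60 gives better precision than promised. This stands. A reader might infer from the mismatch that 60 is too few for the study's main estimate; step 2 shows the opposite for detection.

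Five confounders is a maximum, and the Statistical analysis section fixes neither model nor covariates. A reader might infer that a six-variable logistic model is firmly planned and will be overfitted. The document supports only a risk, should the ceiling be used. The five-plus-one structure also fits the therapeutic-gain comparison more naturally than detection, for which no single exposure is named; the 3.0–3.2 figure is therefore an illustration at the ceiling.

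Ten events per variable is itself a rule of thumb and is not stated in the document. It is used here as the direct counterpart of the rule that is. Relaxing it to five still needs 95–100 patients at 30–32%. The smaller-group count applies to a dichotomised outcome; an ordinal ILAE/Engel analysis keeps somewhat more information, and the document does not allow that gain to be quantified. Linear regression could suit continuous MRI measures, but these are not primary outcomes.

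Calling the approach pragmatic, and leaving power open, concedes uncertainty. It corrects neither the rule nor the denominator. Nor is this a detail left to a fuller document: the derivation is stated, and its premise does not match the stated outcomes.

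**Conclusion.** The justification is wrong as written. The multiplication is correct; the rule belongs to a different kind of outcome and, for seizure outcome, is applied to the wrong number of patients. For detection at the document's 30–32%, the six-variable ceiling has 3.0–3.2 events per variable, and 5.0 in the best case, against the 10 that the rule intends. For seizure outcome the firm conclusion is that 60 enrolled falls short of the linear rule unless all are operated. The range of 0.75–5.0 per variable rests on assumed operated numbers and seizure-free proportions, and on dichotomising the outcome. The detection-rate estimate is sound at N = 60. The error lies in the stated rationale for N and in the promise of adjustment; it does not show that the trial must be enlarged.

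**What to change.** In the Sample size section, delete the linear-regression justification and the claim that 60 allows correction for five confounders, and align the Challenges section. State that 60 is chosen for feasibility and for the precision of the detection rate (half-width about 0.13 at worst).

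For the regressions:
- Detection: limit unpenalised models to about one pre-specified predictor (two only under a relaxed rule, since 19/2 = 9.5 events each).
- Seizure outcome: set the number of predictors by the operated patients and events actually observed.
- Any larger adjusted model, including UHF status plus confounders: use Firth or ridge-penalised regression (logistic or ordinal), labelled exploratory.

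The cost is rewording and a smaller model, with no extra patients. The downside is a less ambitious stated adjustment: confounding in the therapeutic-gain comparison would be addressed only in an exploratory way, and the text should say so.
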